## Methods

### Study Design

The CALM Study was a prospective cohort study that followed first-year undergraduate students for 108 days (September 2-December 19, 2025) during their transition into their first academic term at university. Participants were onboarded between August 25 and September 5, 2025. The study employed a hybrid panel-burst design to capture both longer-term changes across the semester and short-term, day-to-day fluctuations in depressive symptoms and 24-hour movement behaviors. This design is consistent with recommendations for measurement-burst designs that integrate intensive short-term assessment within longer-term longitudinal follow-up to distinguish within-person dynamics from broader developmental change.^45,46^

Participants (N = 144) completed five panel surveys administered at four-week intervals following baseline to assess broader psychosocial and contextual factors across the semester. In parallel, five 7-day intensive daily assessment bursts were distributed across the study period (Days 1–21, 22–42, 43–62, 63–82, and 90–108). The intensive burst design was selected as it optimally balances long study windows with reduced participant burden in smartphone-based research.^47^ Burst timing was randomized within predefined calendar windows and did not align systematically with panel survey administration. No bursts were scheduled during Fall break (Days 83–89) to avoid confounding assessments with atypical routines and travel-related disruptions.

To minimize systematic timing effects across the academic term while preserving calendar balance, burst timing was randomized using a constrained block allocation schedule. The 108-day study was divided into five consecutive calendar periods (four 20–21 day windows during the semester and a final 19-day window following fall break). Each period contained three potential 7-day burst windows corresponding to Early, Mid, and Late segments of the period (Fig. 1). Participants were assigned to one of six pre-specified burst sequences (S1-S6), each representing a unique ordering of Early, Mid, and Late burst timing across the five study periods. A fixed set of sequences was used to ensure exact balance across burst positions while maintaining feasibility within the study platform. This allocation scheme was developed to satisfy the feasibility and balance constraints outlined in Table 1.

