#### Aim 3 (Periods of Heightened Risk for Symptom Onset and Progression).

To examine the temporal stability of the depression symptom network across the first college term, including 24-hour movement behaviors and anxiety symptoms as nodes, time-varying network analyses will be conducted using rolling 7-day calendar windows across the 108-day study period.^103^ Although participants contributed data during assigned burst weeks only, pooled daily observations across individuals provide coverage spanning the full academic term. Within each window, mlVAR models will be estimated to derive temporal (lagged) and contemporaneous networks while accommodating the unbalanced repeated-measures structure of the burst design. Window-specific network metrics, including global connectivity (e.g., average edge weight), network density, and node centrality indices, will be computed to evaluate changes in overall interconnectedness and node influence over time. Periods characterized by increased network connectivity or heightened centrality of specific symptoms or behaviors will be interpreted as potential windows of increased vulnerability – or, conversely, relative stability – during the transition to college. Calendar-based academic or institutional events (e.g., midterm periods, finals week, university-designated mental health initiatives such as Wildcat Pause Day) will be descriptively overlaid onto temporal network estimates to contextualize observed patterns.

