As with all longitudinal research in emerging adult populations, several limitations warrant consideration. First, the sample was drawn from a single university and was predominantly White, with relatively few first-generation status college students, which may limit generalizability to more diverse populations of emerging adults transitioning to college. Second, although wearable devices enable continuous free-living monitoring of 24-hour movement behaviors, reliance on proprietary heart rate-informed classification algorithms may introduce measurement imprecision relative to open-source processing of research-grade accelerometry. However, because the present analyses emphasize within-person associations, systematic classification differences are unlikely to meaningfully bias the primary inferences. Third, while mlVAR modeling allows estimation of temporal associations and separation of within- and between-person effects, these analyses do not establish causality; observed lagged relationships should therefore be interpreted as hypothesis-generating. Additionally, although the burst design enhances feasibility and reduces participant burden, intensive symptom assessment occurred during discrete weeks rather than continuously across the semester. As a result, short-lived fluctuations outside burst windows may not have been captured, and temporal inferences rely on pooled observations across individuals. Fourth, daily assessment of suicidality was excluded from the intensive burst protocol due to ethical considerations and the absence of real-time clinical monitoring during unsupervised reporting. Although necessary, this limited examination of the full range of depressive symptoms represented in the PHQ-9 and Diagnostic and Statistical Manual of Mental Disorders, Fifth Edition. Finally, sustained engagement with repeated panel surveys, intensive daily diary bursts, and continuous wearable monitoring across an academic semester may be challenging,^116^ particularly during periods of academic stress or schedule disruption. To mitigate potential attrition and response fatigue, the study incorporated a structured incentive framework, time-limited burst assessments designed to reduce burden, automated reminders within the mobile platform, and routine participant check-ins and personalized prompts delivered by the research team via email.

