## Figures and Tables

**Figure 1 F1:**
[figure not shown]
Daily diary burst timing (Panel A) and randomization schedule (Panel B). Panel A displays the five 7-day burst periods and their timing within the 16-week study, with each period comprising early, mid, and late windows. Panel B illustrates the randomized allocation of burst timing (early, mid, late) for each of the six cohorts (S1-S6) across the five data collection periods (P1-P5).

**Table 1. T1:** Design Constraints and Allocation Properties of the Intensive Burst

Design Constraint	Description
Exact global balance	Across all sequence assignments, Early (E), Mid (M), and Late (L) burst placements occurred equally often.
Exact per-period balance	Within each calendar period, two pre-specified burst sequence groups were assigned to each burst position (E, M, L), ensuring even distribution of assessment load across the five assessment windows.
Participant-level balance	Each sequence maintained a 2-2-1 distribution of burst timing (two assignments to two positions and one to the third), preserving comparable exposure patterns across participants.
Boundary control	Sequences were constructed to eliminate late-to-early transitions across adjacent periods, thereby preventing consecutive burst weeks at period boundaries. This constraint reduced the likelihood of back-to-back assessment weeks, helping to minimize participant burden and support sustained compliance across the semester.
Primacy and recency balance	Two sequences began and two ended with each burst position, reducing systematic timing bias.

**Table 2. T2:** Cohort baseline characteristics.

Participant Characteristics	Mean (SD) or *n* (%)
Age (years)	18.2 (0.4)
Sex (Female)	79 (54.9%)
Race/Ethnicity	
Asian	2 (1.4%)
Black	3 (2.1%)
Hispanic	7 (4.9%)
White	113 (78.5%)
Multiracial	19 (13.2%)
First-Generation Status (Yes)	24 (16.7%)
Parental Education	
Less than high school	1 (0.7%)
High school	11 (7.6%)
Some college/Some University	13 (9.0%)
College/University	62 (43.1%)
Graduate/Professional degree	57 (39.6%)
College of Enrollment	
College of Health and Human Sciences	43 (29.9%)
College of Arts and Sciences	32 (22.2%)
College of Engineering	40 (27.8%)
College of Agriculture	14 (9.7%)
College of Architecture, Planning & Design	6 (4.2%)
College of Business Administration	5 (3.5%)
College of Education	4 (2.8%)
Self-Rated Health	
Fair	16 (11.1%)
Good	54 (37.5%)
Very Good	58 (40.3%)
Excellent	16 (11.1%)
Mental Health Condition Diagnosis	

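### Aim 3 reads differences between 7-day windows as change in one network, but consecutive burst weeks hold disjoint randomised thirds of the cohort; a comparison of the five periods, each with all students, should carry any claim of change

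*Protocol article*

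**What the plan says.** Study Design divides the term into five periods: "Each period contained three potential 7-day burst windows corresponding to Early, Mid, and Late segments of the period". Each student has one burst per period, placed by the sequence to which the student's study number was randomised (Study Protocol). Table 1 adds: "Within each calendar period, two pre-specified burst sequence groups were assigned to each burst position (E, M, L"). It also rules out a Late burst followed by an Early burst in the next period.

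Data Analyses, Aim 3, fits an mlVAR model in each rolling 7-day window, justified by the statement that "pooled daily observations across individuals provide coverage spanning the full academic term". The step between windows is not given. The reading rule is explicit: "Periods characterized by increased network connectivity or heightened centrality of specific symptoms or behaviors will be interpreted as potential windows of increased vulnerability". Academic events such as finals week are overlaid descriptively.

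The Discussion concedes that "temporal inferences rely on pooled observations across individuals". The burst sequence is not mentioned anywhere in the Data Analyses section.

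**The concern.** Aim 3 is meant to say when the symptom-behaviour network tightens during the term. If one week's network is estimated from one group of students and the next week's from another, a rise between them mixes change over time with differences between people. The article itself expects people to differ: Aim 2 builds separate networks by behavioural profile. Person-centring within a window removes differences in students' mean levels but not differences in their lagged or contemporaneous edges.

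Finals week, for example, would be seen in about a third of the cohort and compared with weeks contributed largely by others. Yet every student has a burst in each of P1-P5, so the design contains a comparison in which all students appear on both sides. Aim 3 as described does not use it.

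**Working it through.** **Inputs.** From the article: N = 144, six sequences, five periods, three positions per period, two sequences per position, a 2-2-1 distribution per sequence, no Late-to-Early transition, and 7 diary days per burst. Assumed, because not given: equal sequence sizes, full compliance, standardised variables, and a between-student SD (tau) of a lagged edge from 0.1 to 0.3.

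**1. Allocation.** 2/6 x 144 = 48 students per burst window.

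**2. Shared students.** Within a period each student has one burst, so Early, Mid and Late groups are disjoint. Across a boundary, a shared student would need Late followed by Early, which Table 1 excludes. Full enumeration agrees: 45 five-period sequences satisfy the 2-2-1 and boundary rules, 573 sets of six also satisfy the per-period balance, and in all 573 consecutive burst windows share 0 of 6 sequences.

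**3. Rolling windows.** In one illustrative layout, windows one day apart share on average 88% of their student composition (86% to 100%), and windows seven days apart share 31% on average. Turnover is thus gradual, and complete only between burst-aligned windows. Even there, three 7-day bursts need 21 days while P3 and P4 have 20 and P5 has 19, so in those periods an aligned calendar window can pick up a day or two of the neighbouring group.

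**4. Effect on one lagged edge when the network never changes.** Seven days give 6 lagged pairs, and person-centring leaves 5 degrees of freedom, so the sampling variance per student is about 1/5 = 0.2. For two disjoint groups of 48:

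SD of change = sqrt(2 x (tau^2 + 0.2) / 48); share due to different students = tau^2 / (tau^2 + 0.2).

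| tau | SD, formula | SD, simulated | Share, formula | Share, simulated |
|---|---|---|---|---|
| 0 | 0.091 | 0.092 | 0% | 0% |
| 0.1 | 0.094 | 0.095 | 5% | 5% |
| 0.2 | 0.100 | 0.102 | 17% | 15% |
| 0.3 | 0.110 | 0.119 | 31% | 29% |

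The simulation used 4,000 runs with a constant network.

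**5. Period comparison.** The same 144 students appear in both periods, so a stable student edge cancels: sqrt(2 x 0.2 / 144) = 0.053. The variance ratio to the disjoint contrast is 3 x (tau^2 + 0.2)/0.2, which is 3.15 at tau = 0.1 and 4.35 at tau = 0.3. The factor 3 comes from using 144 students instead of 48; only the remaining 1.05 to 1.45 comes from removing student mix. In the simulation the same-student SD for 48 students rose from 0.092 to 0.100 as tau rose from 0 to 0.3. Divided by sqrt(3), that is 0.053 to 0.058, so the formula is slightly optimistic at high tau.

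**6. Within-student comparison of neighbouring weeks.** No student is in two consecutive burst windows, so this contrast is only indirect, through a joint model with sequence and window terms. It is estimable in all 573 designs, but its variance averages 1.38 to 2.32 times (median 1.58) the sampling variance of the direct contrast. At best it wins when (tau^2 + 0.2)/0.2 > 1.38, that is, tau > sqrt(0.2 x 0.38) = 0.28.

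**The case against.** The strongest reply is that the thirds are randomised. Which students fall in a week is ordinary sampling of persons, and a multilevel analysis with students as random units can carry that uncertainty; how it is displayed may be left to a fuller plan. Aim 3 contains no formal test, its windows are only potential ones, events are overlaid descriptively, and the pooling is disclosed as a limitation.

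Most of this stands. A reader might infer that the windows are systematically biased; the randomisation does not support that. The one qualification is that late enrolment left missing days for S1 and S2 in the first period, so the earliest window is not a clean random third. A reader might also infer that any two neighbouring windows hold different students, which step 3 contradicts.

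Nor can one say that student mix explains most of an apparent peak. A separate constant-network simulation, with assumed heterogeneity, symptom nodes only and a pooled model, put the share at 2-12% for temporal and 32-46% for contemporaneous connectivity. Those figures depend on heterogeneity values the article does not give. Likewise, the chance spread of the 10 students with PHQ-8 of 10 or more across windows concerns symptom levels and has no demonstrated link to connectivity.

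What the reply does not answer is that the article fixes the window, the model within it and the reading of a rise, while its admission about pooling changes nothing in the analysis.

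**Conclusion.** The point holds as a limited one. Between consecutive burst-aligned windows, a change in the network is a contrast between disjoint thirds of the cohort, so chance differences between students are added to movement over time. That follows from the allocation rules alone and needs no attrition. The size does not follow from the article: about 5% to 31% of the variance of a single lagged-edge change under the assumed SD of 0.1 to 0.3, nil without heterogeneity, and in that range smaller than sampling error. Other network metrics may differ.

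The case for changing the plan does not depend on that unknown. Comparing whole periods reduces the variance of a lagged-edge contrast about 3 to 4 fold, and 3 fold of it comes simply from using every student. It would be wrong to conclude that the 7-day analysis is invalid or should be dropped.

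**What to change.** In Aim 3:

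1. Add a comparison of the network across P1-P5, each containing all six sequence groups, with student effects. Rest any claim that connectivity or centrality changed over the term on this comparison.
2. Keep the rolling 7-day windows as a descriptive display for short events, and state that differences between windows include differences between students. Do not adjust a window by subtracting the same students' other four bursts: a true peak of size d in one burst enters that mean with weight 1/4, so it would lower those students' adjusted values in every other period by d/4 and create artificial differences between windows.
3. Obtain window uncertainty, and any no-change reference, by resampling or reassigning whole students and not days.

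The cost is wording and additional model runs; no new data are needed. The drawback is resolution: the period comparison resolves about 20 days instead of 7, so week-long events such as finals remain descriptive.

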#### Baseline Demographic and Health Measures.

At baseline, participants reported demographic characteristics including age, sex, race/ethnicity, college of enrollment within the university, first-generation college status, parental education (proxy for socioeconomic status), residence hall, self-rated health, food security, and home ZIP code. Home ZIP codes were used to classify participants’ rural-urban residence status using established 2020 Rural-Urban Commuting Area (RUCA) codes.^92^

Height, weight, waist circumference, and hip circumference were measured during the laboratory visit. Height and weight were measured using a calibrated Health O Meter Professional 349KLX digital floor scale and stadiometer. Waist circumference was measured using a measuring tape placed midway between the lowest rib and the iliac crest while the participant was standing. Hip circumference was measured using a measuring tape placed at the level of the maximum circumference over the buttocks while the participant was standing with feet together and weight evenly distributed. Body mass index (BMI) was calculated as weight (kg)/height (m ). Waist-to-hip ratio (WHR) and waist-to-height ratio were computed to characterize central adiposity and abdominal fat distribution. Participants were classified as having abdominal obesity if their waist-toheight ratio was ≥ 0.50, consistent with established clinical cutpoints.^93^

Participants also reported current and past mental health diagnoses, psychiatric medication use, chronotype (i.e., individual differences in circadian preference for morning versus evening activity and alertness; Morningness–Eveningness Questionnaire),^94^ PA participation (Exercise Vital Sign),^95^ and resilience (Brief Resilience Scale).^96^ Participants provided personalized academic schedules (daily class hours), which were used to calculate instructional hours per day and identify the timing of key academic assessments (e.g., exams, major assignments). These data were incorporated into the daily time-series dataset to account for academic time demands and assessment timing.

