### Data Analyses

#### Preparation.

Daily time-series datasets will integrate device-based 24-hour movement behaviors (sleep, SB, LPA, and MVPA), depressive symptoms, anxiety symptoms, contextual covariates, and academic load indicators. Prior to analysis, 24-hour movement behavior data will be inspected for zero values. Any observed zeros will be addressed using a log-ratio expectation–maximization (LREM) approach to permit valid compositional transformation.^97^ Daily wake-to-wake wear times will then be normalized to 1,440 minutes using the R package compositions,^98^ ensuring closure of the 24-hour composition. Movement behaviors will subsequently be transformed into isometric log-ratio (ilr) coordinates using sequential binary partitioning procedures.^99^ Four distinct sets of ilr coordinates will be constructed, each specifying a different behavior (sleep, SB, LPA, or MVPA) as the pivot coordinate (ilr ). This pivot approach enables examination of the relative importance of each behavior compared to the remaining components of the composition, while preserving the inherent co-dependence among sleep, SB, LPA, and MVPA.

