Beyond identifying behavior-symptom link specificity, an additional aim of this work is to determine whether shifts in behavioral time-use distributions precede periods of symptom escalation during the transition to college – a developmental window in which subthreshold symptoms may consolidate into clinically significant depressive episodes.^1,2,5^ Network theory suggests that systems may become more densely connected prior to transitions into more severe states,^113,114^ raising the possibility that time-varying symptom-behavior networks could signal emerging vulnerability. This perspective aligns with precision psychiatry initiatives such as WARN-D,^115^ which seek to detect early warning signals of depression using intensive longitudinal designs that integrate self-reports and passive sensing via wearable devices. At the same time, distinct 24-hour movement behavior composition profiles may demonstrate unique symptom-behavior network structures, suggesting that vulnerability processes differ across behavioral phenotypes. By modeling time-varying symptom-behavior networks across an academic semester, the CALM Study aims to evaluate whether changes in behavioral influence or overall network connectivity coincides with high-risk academic periods, and clarify both when and for whom behavioral perturbations are most strongly associated with symptom worsening. Although temporal associations do not establish causality, estimating lagged relationships at the daily level can generate hypotheses regarding modifiable behavioral processes that may destabilize or stabilize symptom networks during this critical developmental transition.

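### The Discussion promises to test when associations intensify in high-risk academic periods, but Aim 3 gives only a descriptive campus-calendar overlay, although students' own assessment timing is in the dataset

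*Protocol article*

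**What the plan says.** Aim 3 (protocol article, Data Analyses) estimates networks in "rolling 7-day calendar windows across the 108-day study period", pooling whichever students are in a burst. It then reads the resulting curves: "Periods characterized by increased network connectivity or heightened centrality of specific symptoms or behaviors will be interpreted as potential windows of increased vulnerability". Campus-wide events such as midterm periods, finals week and a university mental-health day "will be descriptively overlaid onto temporal network estimates to contextualize observed patterns". No contrast between academic and other periods is named.

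The Discussion goes further. Its opening paragraph says the study will test, among other things, when the associations intensify in vulnerable periods. A later paragraph says the study aims to "evaluate whether changes in behavioral influence or overall network connectivity coincides with high-risk academic periods".

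Student-level timing was also collected. Under Baseline Demographic and Health Measures, personal class schedules served to "identify the timing of key academic assessments (e.g., exams, major assignments". On their use, the section says: "These data were incorporated into the daily time-series dataset to account for academic time demands and assessment timing". The Preparation section lists "contextual covariates, and academic load indicators" among the contents of the daily dataset. Nothing in the article uses this timing as a moderator or as a time axis in Aim 3.

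**The concern.** The stated aim and the stated method do not meet. To say that network change coincides with high-risk academic periods, one needs a comparison of those periods with others, and some measure of its uncertainty. A curve with events marked on it supplies neither. The reader would be left to judge by eye whether a rise sits near an event.

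A campus date is also a rough stand-in for academic pressure. Table 2 lists seven colleges of enrolment, so exams and deadlines need not fall on the same days for everyone. The student's own assessment timing can differ between students on one date and within a student across bursts. It therefore allows a within-person comparison, which the Sample Size Calculation section names as the focus of the primary hypotheses. At stake is whether the paper can answer its *when* question with an estimate.

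**Working it through.** The article gives no figure for this point, so there is none to reproduce. The check has three parts.

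**1. Promise against method.** The Discussion uses the verbs test and evaluate for change in high-risk academic periods. The output of Aim 3 is window-specific connectivity, density and centrality, with events drawn over them. No parameter in Aim 3 represents the difference between an academic high-risk period and any other period, so there is nothing to put an interval on.

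**2. Who is in a window.** Inputs are 144 students and five 7-day bursts (Study Design), six sequences, and two sequences at each Early, Mid or Late position in each period (Table 1). Equal sequence sizes and full compliance are assumed.

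- Students per sequence: 144 / 6 = 24. Students per burst position: 2 × 24 = 48.
- Planned diary days: 144 × 35 = 5,040. A typical 7-day window: 48 × 7 = 336.
- Within-burst lag pairs: 48 × 6 = 288 for one burst position, of 144 × 5 × 6 = 4,320 in all.
- Rolling windows: 108 − 7 + 1 = 102. The one that covers the fall break (Days 83–89) holds no diary data.

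Each student has one burst per period, so the Early, Mid and Late positions of a period hold three separate groups of about 48. Windows one day apart share six of their seven days. Windows about a week apart within a period compare largely different students. A rise on the curve can therefore reflect who was sampled as well as when. The Discussion's limitations paragraph acknowledges that inference over time rests on pooling across individuals.

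If finals week falls after the fall break, as one would expect, it lies in the last period (Days 90–108) and so in every student's fifth burst. A finals-week rise could then not be told apart from a burst-number or end-of-study effect on the calendar curve.

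**3. Dilution.** Let X mark a day near the student's own exam and C a day in a campus exam period. If associations change only on X days, a calendar comparison recovers the fraction λ = P(X | C = 1) − P(X | C = 0) of that change. The document gives neither probability. The values below are assumptions that show the range.

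| P(X given C = 1) | P(X given C = 0) | λ |
|---|---|---|
| 1.0 | 0.0 | 1.0 (no loss) |
| 0.9 | 0.1 | 0.8 |
| 0.7 | 0.2 | 0.5 |
| 0.5 | 0.2 | 0.3 |

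Finals week, when exams are largely shared, should lie near the top of the table. Midterms and course-specific deadlines could lie lower. Nothing in the article says where.

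**The case against.** The strongest reply is that Aim 3 concerns calendar time: the stability of the network over the term and the periods when it changes. The overlay is openly called descriptive, and coincidence with a period is what an overlay shows. The limitations paragraph calls lagged results hypothesis-generating, and a condensed article may leave the modelling of an available daily variable to a fuller plan. On this view, own-exam moderation is a further research question.

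Much of this stands. The Aim 3 text makes no claim that it fails to meet, and the rolling windows suit the calendar-time question. But the hypothesis-generating remark concerns causality and does not supply a missing contrast. Nor is the point that detail was left out: the article states a method for academic periods, and that method cannot carry the Discussion's wording.

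Four stronger readings are tempting and are not supported.

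- *That an exam-specific test is planned and is diluted.* The article speaks of high-risk academic periods. Exams enter only through the midterm and finals examples.
- *That students' own dates serve only as a nuisance adjustment.* The text says they account for assessment timing. It does not exclude another use.
- *That some campus event can be matched to most peaks.* The article gives three example events and no count.
- *That own-exam timing brings a large gain in precision.* Suppose 25% of lag pairs are near an own exam. The effective size is 1/(1/1,080 + 1/3,240) = 810, against 1/(1/288 + 1/4,032) = 269 for one calendar window, and √(810/269) = 1.73. But this sets about four weeks of own-exam days (25% of 108 is 27 days) against one calendar week. Four calendar windows give 1,152 against 3,168 pairs and an effective size of 845, so the gain disappears. If instead each student has one exam week (7/108 = 6.5%, about 280 pairs), the effective size is 1/(1/280 + 1/4,040) = 262, again no better than 269.

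**Conclusion.** The point holds as a mismatch with a cheap remedy. The Discussion promises to test and evaluate, while the only stated method for academic periods gives no contrast, estimate or interval. The calendar axis adds two weaknesses: windows about a week apart within a period hold largely different students (about 48 of 144 each, if sequences are equal in size), and campus periods can mix students near and not near their own exams.

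The cost in sensitivity cannot be sized from the document. It is probably small for finals week, and no fold gain should be quoted. The case for own-exam timing is that it yields a within-person estimate with an interval. It does not rest on a smaller standard error. The priority is low: Aims 1 and 2 are untouched, and Aim 3 remains usable as description.

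**What to change.** Add one pooled multilevel model over all bursts to Aim 3. Define in advance an indicator of proximity to the student's own exam or major assignment, for example the three days before it. Enter it as a main effect and as a within-person moderator of the behaviour-symptom associations, with student random effects and adjustment for study period or burst number. Do not enter assessment timing a second time as a separate covariate. Report the moderation estimates with intervals. Because there are 10 + 6 = 16 daily symptom items, name in advance which associations are to be moderated.

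Keep the rolling-window networks and the overlay as descriptive context for change over the term. If the model is not added, reword the two Discussion statements so that they promise description only.

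The cost is one extra model on data already held. Participant-provided schedules may miss deadlines added later, which would attenuate the contrast. The daily academic-demands item offers a cross-check.
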